### Objectives

This paper reports the protocol and analysis plan for the clinical trial NCT05386394, registered on http://clinicaltrials.gov, which implements a multisite, randomized, double-blind, sham-controlled, within-subject crossover design. The trial aims to assess the effectiveness of a-tDCS targeting the left IFG combined with a novel, theoretically driven behavioral naming treatment in improving spoken naming and spelling abilities in individuals with lvPPA or nfvPPA. The overall goal is to bring tDCS combined with spoken naming and spelling therapy from the research lab closer to the clinic. We hypothesize that a-tDCS targeting the left IFG concurrent with spoken naming and spelling therapy will yield superior improvements compared to sham-tDCS (s-tDCS) paired with the same behavioral therapy, with sustained effects for up to 3 months post-treatment and generalization to untrained items as well as broader language and cognitive tasks subserved by the same area of stimulation. Additionally, we aim to evaluate factors already identified as potential predictors of treatment response, including PPA subtype, aphasia severity, cortical and neurofunctional measures, cognitive abilities, genetic markers, lifelong language experience, and demographic variables such as age and sex.

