### Randomization and blinding

As shown in Table 1, following the T1 assessment, participants will be randomly allocated to either Group 1 or Group 2, thereby determining the order of stimulation conditions. Randomization is performed independently for each variant (lvPPA and nfvPPA), employing block randomization with blocks of four participants, and each site performs randomization independently. Within each block, two individuals will be assigned to Group 1 and the other two to Group 2, ensuring balanced allocation across treatment arms within each PPA variant. Randomization ensures a balanced allocation of treatment sequences across participants, thereby controlling for potential order effects and minimizing biases associated with the crossover design (such as period effects and potential carry-over effects, although limited in this study by the washout period of 3 months (Li et al., 2015; Piantadosi, 2024).

Following the allocation, each participant will be assigned 15 unique five-digit codes provided by the manufacturer of the tDCS stimulator upon device programming (one for each intervention day), indicating whether they receive active stimulation (a-tDCS) or placebo (s-tDCS). The codes are necessary to initiate the tDCS delivery device, but do not reveal whether active or sham stimulation is administered. The research team (including therapists and assessors) and participants will be blinded to whether a- or s-tDCS is being administered during each period to maintain a fully blinded study design. The code list will be decrypted upon study completion to identify when each participant received a- and s-tDCS. The specific programming of the tDCS device during the s-tDCS period condition can be found in the tDCS section below.

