### Statistical analysis

This trial investigates whether combining tDCS targeting the left IFG with a tailored spoken naming and spelling therapy improves language abilities and communication in individuals with PPA, with expected benefits extending to untrained tasks and lasting up to 3 months. It also aims to identify predictors of treatment response.

The primary outcomes will be analyzed using a general crossover formulation that considers each follow-up time point, the effects of treatment (s-tDCS vs. a-tDCS), phase (P1 or P2), and their interaction. For each participant, the data will include the order of treatments (s-tDCS in phase 1 and a-tDCS in phase 2, or vice versa) and changes in accuracy from before to after each phase for phonemic accuracy (during spoken naming) and letter accuracy (during spelling) of trained items.

The general crossover analysis will estimate parameters such as intervention effects in each phase and the overall average intervention effect. Estimates of these effects, standard errors, and confidence intervals will be calculated using the generalized estimating equation (GEE) method with robust variance estimation to account for correlations among repeated outcomes across different time points and phases within an individual. *P*-values will be exact and derived by comparing the estimates to the distribution calculated by permuting the order of intervention assignment across patients.

To address potential carryover effects inherent in the within-subject crossover design, a period-by-treatment interaction term will be included in the GEE model. A significant interaction will indicate possible carryover. In this case, follow-up sensitivity analyses will be conducted such as restricting analyses to Period 1 only, to confirm whether the treatment effect is robust. Washout adequacy will also be examined based on baseline performance at each phase.

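### Carryover is judged by a low-powered interaction test, and a Period 1 analysis triggered by that same test cannot confirm that the treatment effect is robust

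*Protocol article*

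**What the plan says.** All of the analysis text is in the Statistical analysis section of the protocol article. The outcome is "changes in accuracy from before to after each phase", so each phase has its own baseline. A GEE model contains treatment, phase and their interaction, and its scope is described without any condition: "The general crossover analysis will estimate parameters such as intervention effects in each phase and the overall average intervention effect".

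The interaction is then used as a flag, and what follows depends on it: "A significant interaction will indicate possible carryover. In this case, follow-up sensitivity analyses will be conducted such as restricting analyses to Period 1 only". The stated aim of that restricted run is confirmation of robustness. No significance level is given for this test. A further check carries no condition: "Washout adequacy will also be examined based on baseline performance at each phase".

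Elsewhere, Randomization and blinding describes carryover as a potential bias, "although limited in this study by the washout period of 3 months". The Objectives hypothesise benefit "with sustained effects for up to 3 months post-treatment and generalization to untrained items". Data collection makes T4 both the 3-month follow-up of Period 1 and the baseline of Period 2.

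**The concern.** The stated rule has two branches, and neither does what it is meant to do.

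- **Interaction not significant.** The natural reading is that carryover is not a problem. The test compares participants with each other, while the treatment effect is estimated within participants. It is much less precise, so it will often miss carryover large enough to matter.
- **Interaction significant.** The Period 1 analysis is presented as a check on robustness. It uses the same Period 1 data that made the interaction significant, so the two results are strongly correlated and the second is not independent confirmation of anything.

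This matters because the trial's own hypothesis makes carryover plausible. The washout is 3 months and the effect is expected to last up to 3 months. Generalisation to untrained words is expected, and the words to be trained in Period 2 are untrained words throughout Period 1 (Therapy stimuli). Any generalised gain still present at T4 enters the Period 2 baseline.

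**Working it through.** **Inputs from the article.** Power is 85% with 120 participants, and the power formula is Φ(effect / standard error − 1.96) (Sample size). The significance level is 0.05 (Abstract). Allocation is 1:1 to two sequences (Randomization and blinding).

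**Assumptions.** The article gives neither rho nor the variance. I take the same standard deviation σ of the period change in both phases, one time point per phase, a normal approximation, a 5% level for the interaction test, and rho from −0.3 to 0.5. Let m be the number per sequence.

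**The plan's own figure.** No target effect or design variance is given, so 85% cannot be recomputed. Solving the formula backwards gives effect / SE = 1.960 + 1.036 = 2.996. This is enough, because σ and the effect size cancel below.

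**Standard errors.** Let D1 and D2 be the a-tDCS minus s-tDCS differences in Period 1 and Period 2.

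- Pooled effect (D1 + D2)/2: SE = σ√((1 − rho)/m)
- Interaction D1 − D2: SE = 2σ√((1 + rho)/m)
- Period 1 effect D1: SE = σ√(2/m)
- SE ratio, interaction to pooled: 2√((1 + rho)/(1 − rho))
- Correlation of the interaction with D1: √((1 + rho)/2)

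**Power of the interaction test** when the true interaction equals the target effect. The noncentrality is 2.996 divided by the SE ratio.

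| rho | SE ratio | Noncentrality | Power | Power at half that size |
|---|---|---|---|---|
| −0.3 | 1.47 | 2.04 | 53% | 17% |
| 0 | 2.00 | 1.50 | 32% | 12% |
| 0.3 | 2.73 | 1.10 | 20% | 9% |
| 0.5 | 3.46 | 0.87 | 14% | 7% |

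If the 85% refers to 120 enrolled and 120 × 0.85 = 102 are analysed, the full-size figures fall to 47%, 28%, 17% and 13%.

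**Period 1 test read only after a significant interaction**, with no treatment effect and no carryover (bivariate normal probability).

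| rho | Correlation with interaction | Rejects, given significant interaction | Both significant, all null trials |
|---|---|---|---|
| −0.3 | 0.59 | 24% | 1.2% |
| 0 | 0.71 | 34% | 1.7% |
| 0.3 | 0.81 | 45% | 2.2% |
| 0.5 | 0.87 | 53% | 2.7% |

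The last column is the conditional rate multiplied by 5%. In this null setting the conditional mean of the Period 1 estimate is still unbiased; only its error rate is inflated. If the target effect is real and the interaction is equally large, the Period 1 estimates that pass the gate average 1.18, 1.37, 1.63 and 1.88 times the true effect.

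**Direction of carryover.**

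- Suppose active stimulation in Period 1 raises the Period 2 list by g at T4, and a share r of that gain survives to the end of Period 2. The later sham change falls by (1 − r)g, D2 rises by that amount, and the pooled effect is inflated by (1 − r)g/2. For illustration only, g = 5 points and r = 0 gives 2.5 points.
- Suppose instead that earlier active stimulation improves learning in the sham period by c. The pooled effect is then diluted by c/2. With c equal to the target effect the estimate halves, and crossover power falls from 85% to Φ(1.498 − 1.96) = 32%. The interaction test misses this in 47% (rho −0.3) to 86% (rho 0.5) of trials.

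**The case against.** The strongest reply is that the article does not use the discredited two-stage procedure, in which the interaction decides which estimate becomes the main result. A reader might infer such a switch, but the text does not support it. The Period 1 run is called a sensitivity analysis, and the success criterion in the Abstract has no condition on the interaction. In a balanced design with equal variances the pooled and interaction estimates are uncorrelated, so the primary test keeps its error rate. A false-positive pooled result, a significant interaction and a significant Period 1 result in the same direction occur together in only about 0.05 × 0.05 × ½ = 0.125% of null trials. This stands, and it limits the point to how carryover is judged.

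A reader might also infer that no Period 1 estimate will be seen unless the interaction is significant. That is not so. The main model yields phase-specific effects with confidence intervals in every case, and only the restricted refit is conditional. This stands too, and it makes the fix easy.

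Third, it would go too far to say that the test has almost no power or that the triggered analysis is always biased. Changes from separate baselines on different 20-word lists may be weakly correlated, and at rho −0.3 power is 53%. Bias in the estimate needs carryover to exist, and its sign is unknown. Separate lists also keep retained Period 1 training words out of the Period 2 outcome.

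Last, baseline performance at each phase could be examined by a between-sequence contrast, and such detail may sit in an analysis plan that is not shown. Its absence is no error. But the wording equally allows a simple comparison of the two baselines, where the decline that the Introduction expects could cancel carryover.

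None of this rescues the stated rule. Non-significance remains weak evidence, and a Period 1 result selected by a correlated test remains unfit to confirm robustness.

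**Conclusion.** The point holds in a limited form, as a change that should be made. The rule can neither rule out carryover nor confirm robustness. At rho 0 to 0.5 it misses an interaction as large as the target effect in 68% to 86% of trials. The Period 1 test that it triggers rejects in 34% to 53% of null cases that reach it, though only 5% of null trials do. At rho −0.3 the corresponding figures are 47% and 24%. These figures rest on the stated 85% power, an assumed rho, equal variances and a 5% level for the interaction. The primary analysis is not invalidated: its type I error is unaffected. What is at risk is the interpretation of the pooled effect, which carryover could inflate or dilute by an amount that the article's figures do not determine.

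**What to change.** In the Statistical analysis section:

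1. State that the pooled within-participant a-tDCS minus s-tDCS effect is the primary result whatever the interaction shows.
2. Report the Period 1 estimate and the interaction, each with its confidence interval, in all cases. Drop the significance trigger and the description of the Period 1 analysis as confirmation. Reported without the trigger, a Period 1 test has its nominal 5% error. Its power at the target effect is modest, at 56%, 43% or 32% for rho 0, 0.3 or 0.5, so the interval should be read rather than the p-value.
3. Define the washout check as a between-sequence comparison at T4 of change since T1 on the Period 2 training list. Those words are untrained at both visits, and disease decline affects both sequences alike under randomisation, so the contrast estimates carryover into the Period 2 baseline directly. It does not capture an effect on later learning, so the interaction interval is still needed.

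The Primary outcome measures section has the word lists presented at every assessment, so no new data are needed. For Level 2 participants this relies on the Level 2 list having been given at T1, as that section implies. The cost is analysis wording and one extra table.

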## Abstract

Primary progressive aphasia (PPA) is a neurological syndrome characterized by the gradual deterioration of language capabilities. Due to its neurodegenerative nature, PPA is marked by a continuous decline, necessitating ongoing and adaptive therapeutic interventions. Recent studies have demonstrated that behavioral therapies, particularly when combined with neuromodulation techniques such as transcranial direct current stimulation (tDCS), can improve treatment outcomes, including the long-term maintenance and generalization of therapeutic effects. However, there has yet to be a phase II multisite study examining the efficacy of tDCS in individuals with PPA. This paper reports the methods and analyses for the clinical trial NCT05386394. A total of 120 adults with non-fluent and logopenic variant PPA will receive a novel spoken Naming and Spelling (NaSp), individuals with semantic variant PPA will be excluded from this trial. Participants will receive NASP therapy over two periods of 3 weeks (Monday through Friday, for a total of 15 non-consecutive days) combined with anodal (a-tDCS) and sham tDCS (s-tDCS). They will be randomly allocated to receive a-tDCS either during the first or second intervention period. The study will be conducted at four sites across the United States and Canada. Outcome measures will be recorded immediately before and after each intervention period, as well as 3 months after each period. Primary outcome measures will be the change in phonemic accuracy in spoken picture naming and letter accuracy in spelling for trained nouns and verbs. Changes from the a-tDCS and s-tDCS periods will be compared to determine the efficacy of tDCS. Primary outcomes will be analyzed using statistical methods that account for repeated measures within participants (namely generalized estimating equations). A significant adjuvant effect of tDCS will be determined if differences in phonemic accuracy and/or letter accuracy immediately following a-tDCS intervention and/or at the 3-month follow-up are greater (at p < 0.05) than those of the s-tDCS intervention. This trial is the first multisite, fully powered, randomized, double-blind, sham-controlled, crossover study of the effectiveness of tDCS as an adjuvant to behavioral treatment for spoken naming and spelling deficits in individuals with PPA. Specific challenges in designing the protocol are considered.

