Despite promising findings from the previous single-site Phase II study using tDCS paired with similar language therapy in PPA (Tsapkini et al., 2018) and other studies from members of our group (Roncero et al., 2017, 2019; Hung et al., 2017; Nissim et al., 2022; McConathey et al., 2017), no multisite Phase II trial has systematically evaluated its efficacy, which is a helpful step to facilitate transfer of tDCS into the clinical environment. This gap is significant given the encouraging learning and generalization effects observed in lvPPA and nfvPPA populations. The present study is designed to address this gap by evaluating the impact of combined tDCS and behavioral therapy on naming and spelling in a well-powered multisite randomized controlled trial (RCT), and by identifying clinical, neural, and genetic predictors of treatment response. A crossover RCT enables each participant to serve as their own control, increasing power and reducing inter-individual variability.

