### Sample size

Based on the crossover design, we calculated that 120 participants with PPA (40 at each of the three sites) are needed to achieve 85% power in detecting the target effect size (e.s.^target^). The power of the design to detect e.s.^target^ using an estimator is calculated as/is Φ(*e.s*_*target*_/√(*rate*_*design*_/*n*) - 1.96), where *rate*_*design*_/*n* represents the standard error squared of the estimator, and Φ is the cumulative distribution of the normal. Plausible values of *rate*_*design*_ and effect sizes are determined based on similar outcomes from previous studies with comparable crossover designs. The estimated 15% dropout rate is based on previous studies involving individuals with PPA undergoing tDCS and language therapy. In prior RCT from members of our team, attrition was ~15% during the first phase, mostly due to unrelated medical issues (Tsapkini et al., 2018). This rate was used to estimate the required sample size.

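### The Period-1-only robustness check is run only after a significant interaction in the same data, so its result is largely driven by the sign of that interaction, and the trigger is weak

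*Protocol article*

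**What the plan says.** The Statistical analysis section puts treatment, phase and their interaction into a GEE model of within-phase change scores. On carryover it says: "A significant interaction will indicate possible carryover. In this case, follow-up sensitivity analyses will be conducted such as restricting analyses to Period 1 only". The stated purpose is "to confirm whether the treatment effect is robust". No significance level is given for the interaction test. For the treatment comparison, the Abstract requires that differences after active stimulation "are greater (at p < 0.05) than those of the s-tDCS intervention".

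Two commitments in the same section carry no condition: effects in each phase are estimated alongside the overall average, with standard errors and confidence intervals, and washout adequacy is examined from baseline performance at each phase. Nothing says that a Period 1 result would replace the primary result.

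The Sample size section says that "120 participants with PPA (40 at each of the three sites) are needed to achieve 85% power".

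**The concern.** A robustness check should be informative whichever way the data fall. Here it is called only when the difference between the Period 1 and Period 2 effects is large, and it then looks at one of the two terms of that difference. The data that fire the trigger have already moved the Period 1 estimate well up or well down. A real effect could be labelled not robust, or an overestimate could be taken as confirmation, through chance alone.

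The trigger is also a between-person contrast. It lacks the precision for which the crossover was chosen (Introduction: "A crossover RCT enables each participant to serve as their own control, increasing power and reducing inter-individual variability"), so a quiet trigger says little about carryover.

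Carryover is a live possibility here. The Statistical analysis section expects benefit to last up to 3 months, and Randomization and blinding relies on a 3-month washout. In a progressive disease an interaction may also be a true change of effect over time. The plan reads it only as possible carryover.

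**Working it through.** **Inputs.**
- From the article: 85% power (Sample size), critical value 1.96 (power formula in the same section), 1:1 sequences (Randomization and blinding), change scores per phase (Statistical analysis).
- Not given: the target effect e and the design variance. The article says only that "Plausible values of *rate*_*design*_ and effect sizes are determined based on similar outcomes from previous studies with comparable crossover designs". The 85% therefore cannot be reproduced forward. Inverted, it gives e/SE(avg) = 1.96 + 1.036 = 2.996, which is the anchor below. The 15% dropout allowance is not needed, because everything is scaled to the stated power.
- Assumed: rho, the correlation of a person's two change scores, from 0 to 0.5, with -0.3 as a contrast; 0.05 two-sided for the trigger; normal approximation; complete data.

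**Algebra.** Let D1 and D2 be the active-minus-sham differences in Periods 1 and 2, avg = (D1 + D2)/2 and I = D1 - D2. Then D1 = avg + I/2 exactly. With n participants split equally and standard deviation s per change score:
- Var(avg) = 2s²(1 - rho)/n, Var(I) = 8s²(1 + rho)/n, Cov(avg, I) = 0
- r = SE(I)/SE(avg) = 2·sqrt((1 + rho)/(1 - rho))
- SE(D1)/SE(avg) = sqrt(1 + r²/4)
- Corr(D1, I) = sqrt((1 + rho)/2), which is 0.71 to 0.87 for rho 0 to 0.5

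**Period 1 given the trigger (true effect e, no carryover).** A standard normal variable above 1.96 averages 2.338. The mean of D1 after a positive trigger is therefore e·(1 + (r/2)·2.338/2.996), and after a negative trigger e·(1 - (r/2)·2.338/2.996). For rho = 0 (r = 2) these are 1.78e and 0.22e. For rho = 0.5 (r = 3.46) they are 2.35e and -0.35e. The conditional significance rates come from simulation.

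**Power of the trigger.** Carryover of size L·e shifts I by L·e and biases avg by -L·e/2. The trigger's non-centrality is 2.996·L/r. For L = 1 this is 1.50 at rho = 0 and 0.87 at rho = 0.5.

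**Power of Period 1 alone.** The non-centrality is 2.996/sqrt(1 + r²/4), which is 2.12 at rho = 0 and 1.50 at rho = 0.5.

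| rho | r | Mean D1/e, positive trigger | Mean D1/e, negative trigger | Period 1 significant for active, negative trigger, effect e | Period 1 significant given trigger, no effect | Trigger fires, L = 1 | Trigger fires, L = 1.5 | Power of Period 1 alone |
|---|---|---|---|---|---|---|---|---|
| -0.3 | 1.47 | 1.57 | 0.43 | 13% | 24% | 53% | 86% | 68% |
| 0 | 2.00 | 1.78 | 0.22 | 2% | 34% | 32% | 61% | 56% |
| 0.3 | 2.73 | 2.06 | -0.06 | under 0.1% | 45% | 20% | 38% | 43% |
| 0.5 | 3.46 | 2.35 | -0.35 | 0% | 53% | 14% | 25% | 32% |

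After a positive trigger at effect e, Period 1 is significant in about 99% of cases in every row. If avg and I are both significantly positive, Period 1 must be: its z is at least 1.96(1 + r/2)/sqrt(1 + r²/4), which exceeds 1.96. In that situation the check cannot fail, so it confirms nothing.

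Carryover with L = 1 lowers the power of the main analysis from 85% to Φ(2.996/2 - 1.96) = 32%. The trigger detects it more often than not only if rho is below about -0.26.

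**The case against.** The best defence is that this is not a test-then-switch rule. The analyses are labelled as sensitivity analyses, and nothing displaces the average effect. A reader might infer that the primary type I error is inflated, as in the classic two-stage crossover procedure. The text does not support that. A reader might also infer that without a trigger there is no Period 1 estimate. That is not so either: phase-specific effects with confidence intervals are promised without condition, and baseline washout is examined regardless. Both points stand, and they reduce the matter to the gate and how the check is read.

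Second, the article does not say that confirming means p < 0.05 in Period 1. The significance rates above depend on that reading. The selected means do not: a Period 1 estimate looked at only after the trigger is shifted however it is judged.

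Third, rho is unknown and could be negative. The 3-month visit after Period 1 is also the Period 2 baseline, so the 3-month changes share that measurement with opposite signs. At rho = -0.3 the pattern is weaker, as the table shows. The stated reason for the crossover, within-person control, points to a positive value.

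Fourth, each period trains its own word list and change is taken from that phase's own baseline, which may limit carryover. This bears on how likely carryover is, not on whether the gated check can detect or judge it.

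**Conclusion.** The point holds in a limited form. The gate makes the robustness check a selected result, largely but not wholly driven by the sign of the interaction. It would go too far to say that the sign settles the verdict whatever the true effect: with no effect, a triggered Period 1 analysis is significant in 34% to 53% of cases for rho 0 to 0.5, far above 5% but not nearly always.

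For the same range of rho, the trigger misses 68% to 86% of carryover equal to the target effect. It does not miss most carryover of every size: at rho = 0 it flags 61% at 1.5 times the effect. These figures rest on the stated 85% power, the assumed rho, a 0.05 trigger level and the normal approximation. At a 0.10 trigger level, carryover equal to the target effect would be flagged in 44%, 30% and 22% for rho 0, 0.3 and 0.5.

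The primary test is unaffected. What is at risk is the claim of robustness, in a trial whose hoped-for duration of benefit equals its washout.

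**What to change.** In the carryover paragraph of the Statistical analysis section:

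1. Remove the condition that ties the Period-1-only analysis to a significant interaction.
2. State that the average crossover effect remains the primary estimate whatever the interaction shows.
3. Always present the Period 1 estimate with its confidence interval beside the average effect as the sensitivity analysis. Compare the two as estimates and not by the Period 1 p-value, since Period 1 alone has only about 32% to 56% power at the planned effect for rho 0.5 to 0.
4. Report the Period 1 minus Period 2 difference with its confidence interval and no significance gate. Describe it as carryover or change of effect with time, and say that this design cannot separate them.

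The cost is a few sentences. The phase-specific effects are already to be estimated, so little or no extra modelling and no new data are needed.

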To identify the predictors of differential effects of tDCS vs. sham on primary outcomes, we will separately analyze clinical (PPA variant, severity of impairments), neural (functional and structural), genetic, cognitive, and demographic (age, sex) factors, as well as lifelong language experience (e.g., bilingualism) factors. We will employ a model comparison approach, evaluating each predictor type based on effect size and cross-validated R-squared variance. By sequentially adding each predictor type, we will measure the variance contributed by each factor and establish a threshold for acceptable variance from each factor. To account for multiple comparisons across the range of predictors tested, we will apply False Discovery Rate (FDR) correction using the Benjamini-Hochberg procedure (Benjamini and Hochberg, 1995). This approach controls the expected proportion of false positives among the predictors identified as significant, ensuring a balanced trade-off between Type I error control and discovery potential in the context of exploratory modeling.

Using cross-validated, R-squared model selection minimizes the need for extensive adjustments for multiple comparisons. We will also assess the significance of the remaining factors by comparing them to the bootstrap distribution of sorted t-statistics under the null hypothesis that no factors predict the tDCS vs. sham effect. This final model will help us identify individuals who demonstrate a statistically significant difference between the effects of tDCS and sham treatment.

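### The predictor analysis promises to identify individuals with a significant tDCS-sham difference, which one active and one sham period per person cannot show, and it wrongly treats cross-validated selection as easing multiplicity

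*Protocol article*

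**What the plan says.** The Statistical analysis section of the protocol article sets out how predictors of the tDCS-sham difference will be found. Predictor types (clinical, neural, genetic, cognitive, demographic, language experience) are added in sequence and judged by effect size and cross-validated R-squared. A BH false discovery rate correction is applied over the predictors tested, and the modelling is called exploratory.

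The next paragraph opens: "Using cross-validated, R-squared model selection minimizes the need for extensive adjustments for multiple comparisons". It goes on to say that the analysts will also "assess the significance of the remaining factors by comparing them to the bootstrap distribution of sorted t-statistics", under a null in which no factor predicts the difference. It closes: "This final model will help us identify individuals who demonstrate a statistically significant difference between the effects of tDCS and sham treatment".

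On the design, Trial design and settings gives each participant one active and one sham period, in randomised order. Therapy stimuli assigns a separate 20-word trained list to each period. The Introduction says that gradual decline is to be expected during the intervention period.

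**The concern.** Two statements in this section are not supported.

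**Individuals.** To say that a given person demonstrates a significant difference, that person's own noise must be known. Neither condition is repeated within a person, so one active-minus-sham contrast mixes true response with day-to-day variation, that person's decline between periods, and how hard the two word lists happen to be for them. The 20 words in a list are replicate items, not replicate periods.

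**Multiplicity.** Choosing factors by predictive fit and then testing them on the same data does not reduce the need for adjustment. Selected factors tend to have large t-statistics because they were selected. Whether the later tests are valid depends on whether the null distribution and the BH count cover the whole search, and the text does not fix this.

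The Conclusions hope that the work could help clinicians identify who is most likely to benefit. A chance predictor, or a list of individuals called significant, would mislead that later use.

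**Working it through.** **Part 1: what one participant's contrast can show**

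Inputs, from Sample size and the Abstract:
- Size: "we calculated that 120 participants with PPA (40 at each of the three sites) are needed". The stated power is 85%.
- Power = Φ(es/√(rate/n) − 1.96). The 1.96 corresponds to a two-sided 5% level, and the Abstract's criterion is p < 0.05.
- Dropout of 15%, so 120 × 0.85 = 102 completers if 120 is the number enrolled.
- Effect size and rate are not printed. The article says only that "effect sizes are determined based on similar outcomes from previous studies with comparable crossover designs".

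The 120 / 85% pair therefore cannot be reproduced, but the ratio it implies can be solved for:
- es/√rate = (1.96 + 1.036)/√120 = 0.274
- If the 85% refers to 102 completers: 2.996/√102 = 0.297

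Putting n = 1 into the same formula and adding the opposite tail for the two-sided value:

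| Quantity | 85% at n = 120 | 85% at n = 102 |
|---|---|---|
| Two-sided power for one person | 5.9% | 6.0% |
| Chance that the observed difference favours sham although all benefit equally, Φ(−ratio) | 39% | 38% |
| Ratio needed for 80% power in one person (1.96 + 0.84 = 2.80), as a multiple of the implied ratio | 10.2 | 9.4 |
| Participants flagged by a 5% individual test with no effect at all | 6 of 120 | 5 of 102 |

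These figures treat the whole per-person spread as noise. If part of it is true variation in response, the noise is smaller, but the design offers no way to tell how much.

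**Part 2: the selection step**

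The number of candidates and the selection threshold are not stated, so the following are assumptions. The main simulation used 102 participants, independent predictors with no effect, forward selection by 10-fold cross-validated R-squared, and at most 5 factors kept. Bootstrap results rest on 400 trials of 99 resamples; the 30-candidate run had 300 trials and no bootstrap. Entries are the chance of at least one false predictor.

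| Procedure | 10 candidates | 20 | 30 |
|---|---|---|---|
| All candidates tested, no selection, no adjustment (1 − 0.95^m) | 40% | 64% | 79% |
| Unadjusted tests on selected factors | 42–47% | 71–74% | 87% |
| BH counting selected factors only | 24–28% | 38–40% | 50% |
| Bootstrap on selected factors only | 29.5% | 38.3% | not run |
| BH counting all candidates | 5–7% | 9% | 7% |
| Bootstrap repeating selection in each resample | 5.7% | 4.8% | not run |

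A second simulation (120 participants, 5-fold cross-validation, a gain above 0.005 to enter, at most 6 factors, 199 permutations on the selected factors only) gave 25% with 10 candidates and 31–33% with 20.

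The first two rows bear directly on the selection rationale: after cross-validated selection, unadjusted testing is no safer than testing every candidate without adjustment. The last four rows show that scope decides the result.

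**The case against.** **On individuals.** Order is randomised, phase is in the model, and lists are matched on age of acquisition, frequency and length, so average period and list effects are handled. The closing sentence says only that the model will help, no responder test or cut-off is specified, and the Conclusions speak of people most likely to benefit. It may be loose wording for covariate profiles. This stands in part: a reader might infer that participants will be formally labelled as responders, and the article sets no such rule. But controlling averages does not remove person-specific variation. The Discussion itself notes that items are not chosen on baseline performance and that a trained list may mostly hold words a participant already finds easy. The literal claim remains unsupported.

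**On multiplicity.** A reader might infer that the plan tests only the factors that survive selection and so will report chance predictors. The text does not support that. BH is stated over the predictors tested, the bootstrap is an additional step, its null is global, and nothing says that it leaves selection out. That detail may sit in an analysis plan not shown here. A reader might also see a flat contradiction between the FDR sentence and the selection sentence. The latter plays down extensive adjustment without ruling out adjustment, so the two sit uneasily together but do not exclude each other.

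**On size.** The simulations select single factors, whereas the plan adds predictor types, and their stopping rules are assumed. Nor does the article say that every pairwise connectivity measure enters the model, so a much larger candidate count should not be inferred. The error rates illustrate the mechanism; they do not forecast this trial's results.

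**Conclusion.** The point holds in two limited parts.

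1. The claim to identify individuals with a significant difference exceeds what one active and one sham period can show. At the signal-to-noise ratio implied by the protocol's own sample size, a single person's contrast has about 6% two-sided power, barely above the 5% error rate. This rests on reading the design's variance rate as per-person noise.
2. The rationale that cross-validated selection lessens the need for adjustment is wrong. The harm is conditional. If the bootstrap or BH covers only the remaining factors, the chance of a false predictor under a global null is roughly 25–40% with 10–20 candidates. If selection is repeated in each resample it is about 5%, and if BH counts all candidates about 5–9%. The candidate counts, independence of predictors and selection rules are assumed.

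It would be too strong to treat prediction as half of the trial's purpose: Objectives introduces it as an additional aim, and the analysis is labelled exploratory. The primary comparison is unaffected. The changes should still be made, because the predictor aim otherwise rests on an unattainable claim and a false justification.

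**What to change.** - Replace the closing sentence with a commitment to report the predicted average tDCS-sham difference by covariate profile, with intervals, and to compare predicted with observed differences on held-out folds.
- Delete the sentence that selection lessens the need for adjustment.
- State that every bootstrap resample repeats the whole procedure, including selection, and that the sorted t-statistics are compared with that distribution.
- State that BH counts all candidate predictors examined, not only those kept.

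No change to design, sample size or data collection is needed. The cost is wording, more computing time, and fewer predictors called significant.
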